## Abstract

**Background:**

Catheter-associated urinary tract infection (CAUTI) is one of the most common hospital-acquired infections. However, many cases treated as hospital-acquired CAUTI are actually asymptomatic bacteriuria (ABU). Evidence-based guidelines recommend that providers neither screen for nor treat ABU in most catheterized patients, but there is a significant gap between these guidelines and clinical practice. Our objectives are (1) to evaluate the effectiveness of an audit and feedback intervention for increasing guideline-concordant care concerning catheter-associated ABU and (2) to measure improvements in healthcare providers' knowledge of and attitudes toward the practice guidelines associated with the intervention.

**Methods/Design:**

The study uses a controlled pre/post design to test an intervention using audit and feedback of healthcare providers to improve their compliance with ABU guidelines. The intervention and the control sites are two VA hospitals. For objective 1 we will review medical records to measure the clinical outcomes of inappropriate screening for and treatment of catheter-associated ABU. For objective 2 we will survey providers' knowledge and attitudes. Three phases of our protocol are proposed: the first 12-month phase will involve observation of the baseline incidence of inappropriate screening for and treatment of ABU at both sites. This surveillance for clinical outcomes will continue at both sites throughout the study. Phase 2 consists of 12 months of individualized audit and feedback at the intervention site and guidelines distribution at both sites. The third phase, also over 12 months, will provide unit-level feedback at the intervention site to assess sustainability. Healthcare providers at the intervention site during phase 2 and at both sites during phase 3 will complete pre/post surveys of awareness and familiarity (knowledge), as well as of acceptance and outcome expectancy (attitudes) regarding the relevant practice guidelines.

**Discussion:**

Our proposal to bring clinical practice in line with published guidelines has significant potential to decrease overdiagnosis of CAUTI and associated inappropriate antibiotic use. Our study will also provide information about how to maximize effectiveness of audit and feedback to achieve guideline adherence in the inpatient setting.

**Trial Registration:**

NCT01052545

## Background

Urinary tract infection (UTI) is the single most common hospital-acquired infection, and many cases of nosocomial UTI are associated with an indwelling urinary catheter [1,2]. Urinary catheters bypass normal host defenses, and bacteriuria develops at the rate of approximately 5% per day; [3] nearly all individuals (98%) who are catheterized for 30 days or longer will have bacteriuria caused by one or more species of potentially pathogenic bacteria [4,5]. Furthermore, organisms causing catheter-associated urinary tract infection (CAUTI) are frequently resistant to one or more antibiotics [6,7]. In addition to these concerns regarding quality of care, annual incremental costs attributed to nosocomial CAUTI in 2002 were estimated to exceed $451 million [8]. Finally, since public reporting of nosocomial infections has become mandated in more than 30 states, [9] hospitals have strong incentive to reduce their rates of hospital-acquired CAUTI.

An important distinction exists between CAUTI and asymptomatic bacteriuria (ABU). CAUTI, as defined by the US Centers for Disease Control (CDC) and the National Healthcare Safety Network, involves symptoms (fever, urgency, frequency, dysuria, or suprapubic tenderness), in addition to microorganisms in the urine [10]. CAUTI requires antimicrobial treatment to relieve symptoms, while patients with ABU are, by definition, asymptomatic. Treatment of ABU in patients with an indwelling catheter does not improve morbidity or mortality, nor does it decrease the incidence of symptomatic CAUTI [11]. Use of antimicrobial agents to prevent or to treat catheter-associated ABU does lead to emergence of resistant flora, however [12]. Accordingly, evidence-based guidelines concerning ABU have stated that it is inappropriate to screen for or to treat ABU associated with the presence of a urinary catheter, with the exceptions of pregnant women and persons undergoing invasive urologic procedures [11,13]. The CDC campaign to prevent antimicrobial resistance in hospitalized patients likewise instructs clinicians to "treat infection, not colonization." [14] Unfortunately, a significant translation gap between evidence-based guidelines concerning management of ABU and clinical practice has been observed throughout the world [15,16]. Overtreatment of ABU is a quality, safety, and cost issue, particularly as unnecessary antibiotics lead to emergence of resistant pathogens [14,17].

Audit and feedback, or providing healthcare professionals with timely data about their performance, has proven efficacy as a means to improve quality of care [18,19]. Two systematic reviews of audit and feedback concluded that there was no evidence that multifaceted interventions worked better than did audit and feedback alone [18,19]. These reviews also suggest that the structure of the intervention should be tailored to the local setting and that the intensity of feedback should be high. More specific information about elements of effective audit and feedback emerges from a qualitative survey of the Department of Veterans Affairs (VA) facilities with either high or low adherence to six clinical practice guidelines [20]. VA facilities with a high level of guideline compliance provided feedback that was frequent/timely, individualized, nonpunitive, and in some cases, customizable. Additionally, providing the correct solution in the feedback appeared to be important [21]. We plan to build upon these findings using audit and feedback first at the individual level and later at the level of the hospital ward team to improve the implementation of ABU guidelines into routine care.

### Primary objectives and hypotheses

#### Objective 1

The first objective is to improve quality of care concerning catheter-associated ABU, in terms of clinical outcomes through implementation of an audit and feedback strategy at the intervention site. Clinical outcomes will also be monitored at the control site. Both sites are tertiary care VA hospitals. We hypothesize that improving adherence to evidence-based guidelines concerning ABU will decrease the inappropriate use of antibiotics to treat catheter-associated ABU (objective 1a) and will decrease inappropriate screening for ABU (objective 1b).

#### Objective 2

Our second objective is to measure increases in clinicians' knowledge of and attitudes towards practice guidelines associated with the intervention. Domains of knowledge measured will include awareness of and familiarity with ABU guidelines. Domains of attitudes measured will include acceptance of and outcome expectancy regarding nontreatment of ABU. We hypothesize that successful implementation of the intervention will improve clinicians' knowledge of and attitudes towards the guidelines.

## Methods

### Study design

The study uses a controlled pre/post design to test an intervention using audit and feedback of healthcare providers to improve their compliance with ABU guidelines. The intervention and the control sites are two different VA hospitals.

### Conceptual framework

The conceptual framework for our study (Figure 1) has been adapted and updated from the Cabana *et al. *[22] model of barriers to physician guideline adherence to focus on the following issues: awareness and familiarity (knowledge), acceptance and outcome expectancy (attitudes), and external barriers [22,23]. The first external barrier that we will address is that the various definitions of CAUTI and catheter-associated ABU are obscure, conflicting, and difficult to apply to hospitalized patients. The ABU and CAUTI guidelines lack specific information about how to apply the definitions of ABU and CAUTI to individual patients. We will provide this clarity by developing a diagnostic algorithm to distinguish between CAUTI and ABU.

**Figure 1 F1:**
[figure not shown]
**conceptual model for treatment of asymptomatic bacteriuria (ABU) and patient health outcomes**. Our conceptual model adapts and updates elements of the Cabana model of "Why don't physicians follow clinical practice guidelines?" to focus on the following barriers to guideline implementation: awareness and familiarity (knowledge), agreement and outcome expectancy (attitudes), and external barriers (behavior). The audit-feedback intervention will tackle 2 points in the chain of events that leads from a patient at risk to a patient who receives unnecessary antibiotics for ABU: the decision to order a urine culture (inappropriate screening) and the decision to treat a positive urine culture (inappropriate prescribing). We can measure the clinical outcomes after each of these points (objective 1), and at the same time we can measure changes in providers' awareness, familiarity, acceptance, and outcomes expectancy of ABU guidelines (objective 2). This conceptual model will help us determine which aspects of our implementation protocol are responsible for the observed changes in clinical outcomes.

Distributing this guidelines-based algorithm will address both awareness and familiarity, but guideline dissemination alone is not an effective method to achieve guideline implementation [18,19,24-26]. The audit and feedback intervention will tackle two points in the chain of events that leads from a patient at risk to a patient who receives unnecessary antibiotics for ABU: the decision to order a urine culture (inappropriate screening) and the decision to treat a positive urine culture (inappropriate prescribing). We can measure the clinical outcomes after each of these points (objective 1); at the same time, we can measure changes in providers' knowledge (awareness and familiarity) and attitudes (social norms, acceptance, risk perceptions, self-efficacy, and outcome expectancy of ABU guidelines) (objective 2). The algorithm itself and the instructions on how to use it (via audit and feedback) will address self-efficacy concerning the guidelines. Lack of outcome efficacy will also be addressed through the audit and feedback sessions, as clinicians will be reassured when they see that withholding inappropriate antibiotics does not lead to harm and may even benefit their patients. We expect agreement with and acceptance of guidelines to likewise increase. We will also identify external barriers to guideline compliance by performing exit interviews with clinicians who have participated in the study. The conceptual model depicted in Figure 1 will enable us to determine which aspects of our implementation protocol are responsible for the observed changes in clinical outcomes.

### Study timeline

Our study will occur over three years (see Table 1). Year 1 will be the development phase, year 2 will involve the implementation of the intervention and the initial pre/post evaluation, and year 3 will provide follow-up and evaluation of the sustainability of the intervention. Throughout the three years of the study, we will perform surveillance at both sites for the clinical outcomes that are the focus of objective 1. Specific hospital units with low levels of guideline-concordant behavior and high clinical need for the intervention will be the focus of our strategy. Also during the first year we will develop the educational study materials and surveys that will be used during the second and third years of the study. These study materials include the CAUTI diagnostic algorithm, the audit and feedback intervention and script, and the surveys to be administered before and after the intervention.

**Table 1 T1:** overview of study activities at intervention and control sites

Year	MEDVAMC (intervention)	STVHCS (control)
Year 1	Baseline surveillance	Baseline surveillance
	Development of study materials (algorithm, surveys, and audit and feedback script)	
	Qualitative data collection on study materials	

Year 2	Ongoing surveillance	Ongoing surveillance
	Guidelines distribution (algorithm)	Guidelines distribution (algorithm)
	Intervention: individual audit and feedback	
	Pre/post surveys	

Year 3	Ongoing surveillance	Ongoing surveillance
	Guidelines distribution (algorithm)	Guidelines distribution (algorithm)
	Intervention: unit-level feedback	
	Pre/post surveys	Pre/post surveys

The intervention will begin in year 2. We will distribute guidelines and definitions concerning ABU and CAUTI at both sites in the form of a diagnostic algorithm. Guideline distribution to providers will continue at appropriate intervals at both sites for the ensuing two years. During the second year, we will provide individualized audit and feedback at the intervention site. The research team will review episodes of bacteriuria and the management implemented by the provider who ordered the urine culture. Research personnel will then visit the provider to discuss whether his or her behavior was or was not in compliance with ABU guidelines. Unit-level feedback will also be given by the research assistant on a monthly basis by presenting the unit's results in graphical form. The unit in this case will be the five hospital wards for the long-term care patients and the eight internal medicine teams for the medicine wards. At the control site, algorithm distribution alone will occur during the second year. During the second year, we will also evaluate the effect of the intervention on the barriers to guidelines implementation in terms of awareness, familiarity, acceptance, and outcome expectancy through pre/post surveys completed by healthcare providers at the intervention site. Exit (qualitative) interviews with study participants will also address potential barriers to implementation of our intervention protocol.

During the third year of the study, the individualized visits to providers will cease, but unit-level feedback will continue over the course of the third year at the intervention site. During this year, the surveys will be administered at the control site in addition to the intervention site so that we can assess the effect that the surveys alone have on prescribing behavior and on responses to survey questions. The purpose of the third year is to continue to measure elements of the study, as well as to evaluate issues of sustainability and the minimal intervention elements needed for dissemination.

### Setting and participants

#### Setting

The intervention site and the control sites were chosen because they are alike in terms of ward organization, patient population, infection-control software, and clinician and medical resident involvement in patient care. We also studied the organizational context of the proposed intervention site (MEDVAMC) and control site (STVHCS) using the results of the VA Clinical Practice Organizational Survey (CPOS), Chief of Staff Module, with specific focus on responses to survey elements concerning support for guideline adherence and implementation of quality improvement measures [27]. Overall, the two sites are similar in several key elements relevant to our project. In particular, audit and feedback is not used extensively at either site and is primarily applied to clinicians' laboratory test ordering. Both sites rely on designated site champions to implement clinical guidelines or performance measures, although finding someone willing to take on this role was difficult at one of these sites because of time constraints. The leaders at both sites are strongly committed to continual improvement.

We believe that a hospital-wide intervention will be necessary (as opposed to intervening at the ward level) because medical residents travel throughout the hospital via consult services and thus, may potentially serve to diffuse knowledge throughout the facility. Hospital units at the intervention site with the highest rates of guideline-noncompliant behavior were identified, including the five general medicine wards and the five extended-care units, where 36.1% of patients received inappropriate treatment. The corresponding units at the control site have been selected for our study (three medicine wards and two extended-care wards). The intervention and control facilities are in different Veterans Integrated Service Networks, or VISNs, which is advantageous for study purposes. For the STVHCS to be a true control, healthcare providers should not overlap or have significant work-related communication with the intervention facility. Also, performing the study in two different VISNs will ultimately facilitate diffusion of the study intervention.

### Participants

#### Research team

The research team brings together a diverse group of members from both sites. The nine investigators include three infectious diseases physicians, a geriatrician, a biostatistician, a measurement psychologist, a health economist, and two industrial/organizational psychologists. Each site has a research assistant, with oversight provided by the overall research coordinator for the study. A programmer works with the team to code the database, and the research site has dedicated personnel for research-compliance assurance.

#### Healthcare providers targeted in the intervention

The audit and feedback intervention will be applied to the healthcare providers who make the decision to treat CAUTI. The healthcare provider who makes the decision to order a urine culture and to prescribe antibiotics for a positive urine culture differs depending on hospital unit. In the internal-medicine wards, this decision is made by internal-medicine residents, who are usually either interns or second-year residents (postgraduate year 1 or 2). Approximately 170 medical residents rotate through the intervention site medicine wards per year. The extended-care units are staffed by nurse practitioners and physician assistants, with supervision provided by VA staff physicians trained in geriatrics. Therefore, in the extended-care ward, the intervention will target the nurse practitioners, physician assistants, and staff physicians, currently 17 individuals.

#### Patients participating in the study

All patients in the targeted study wards at the two sites are indirectly participating in the study through our surveillance for relevant clinical outcomes. Year 1 of the study began in July 2010, so we are currently in the baseline surveillance phase. Reviews of the medical records are performed for all patients in the study wards at both sites five days per week; weekend surveillance results are captured backwards from Monday's findings. This review is performed using the VA electronic medical record, the Clinical Patient Record System (CPRS). Information collected includes bed-occupancy days, presence of any type of urinary catheter (indwelling or Foley, external or condom, intermittent, and suprapubic), whether a urine culture was sent, and the results of any urine cultures sent. Bedside visits are made in one ward per month to verify the catheter presence and type reported in the electronic medical record. Additional information is collected for each episode of bacteriuria (≥10^3 ^organisms/mL of urine). For each episode of bacteriuria, we collect information about patient demographics, the presence/absence of relevant symptoms and comorbidities, and type/duration of antibiotics given. We use this information to classify episodes of bacteriuria as ABU or CAUTI and to determine whether the provider's response to the urine culture results was appropriate or inappropriate. Surveillance data are stored in Excel (Microsoft Corporation, Seattle, WA, USA), while the individual episodes of bacteriuria are detailed in an Access database (Microsoft Corporation, Seattle, WA, USA), which also uses a computer query to verify our case classification. We use Theradoc^® ^(Hospira, Inc., Salt Lake City, UT, USA), a proprietary infection-control software package used in several VA hospitals, to extract the information about antibiotic usage from CPRS.

### Intervention

#### Development of intervention components

As the study is currently in year 1, we are developing, piloting, and validating the following study materials to be used in the intervention: a diagnostic algorithm for CAUTI versus ABU, the audit and feedback script and intervention, and the pre/post surveys (described in Data collection below) of guidelines knowledge and attitudes (see Tables 1 and 2).

**Table 2 T2:** outcome measures for objective 2

Outcome	Measurement strategy	Measure of meaningful change
Guidelines awareness	Survey questions KA1-KA2^a^	Raw number and proportion of respondents changing from NO to YES

Guidelines familiarity	Survey question KF1 ^a^	Average increase from "do not recall" or "minimal recall" to "working familiarity" or "complete recall"

Guidelines familiarity	Survey questions KF2-KF8	Raw number and proportion of respondents changing from SD or D to SA or A

Guidelines familiarity	Survey question KF9	Raw number and proportion of respondents changing from incorrect to correct answers

Guidelines acceptance	Survey questions AA1-AA2 ^a^	Raw number and proportion of respondents changing from SD or D to SA or A

Outcomes expectation	Case scenarios OE1-OE6	Raw number and proportion of respondents changing from incorrect to correct answers

Implementation performance measures	Qualitative exit interviews	≥75% positive statements
	Capture of episodes of bacteriuria	≥95% capture of episodes of bacteriuria
	Delivery of audit and feedback	≥80% delivery to correct provider

^a^KA measures knowledge awareness, KF measures knowledge familiarity, AA measures awareness acceptance, and OE measures outcome expectancy.

A = agree; D = disagree; SA = strongly agree; SD = strongly disagree.

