For the remaining dependent variables identified in Table 3, when possible, we will test for differences between the intervention and control using the hierarchical regression approaches above. For rare outcomes for which fewer than 10 total cases are expected, we may be unable to conduct comparative analyses and will instead provide descriptive analyses.

#### Analysis plan and sample size for objective 2

We expect to survey 100 providers at the MEDVAMC in year 2, 100 providers at the MEDVAMC in year 3, and 100 providers at the STVHCS in year 3, resulting in 300 paired pre/post surveys. We will calculate the raw number and proportion of providers at each site whose survey responses exhibit clinically meaningful change (provider learning), as described in Table 2. Though we recognize that this measurement process will be exploratory, we expect the results to shed light on the efficacy of the intervention from a provider perspective, triangulating with improved clinical outcomes from objective 1 and thus augmenting our overall rationale for dissemination. We also intend to explore which of the attributes measured in objective 2 are associated most strongly with changes in clinical outcomes measured in objective 1 and to assess how well any empirical relationships are supported conceptually. Finally, we will assess the empirical relationships between provider learning and provider demographics.

To measure the success of the audit and feedback system, we will document how many episodes of bacteriuria were audited (underwent medical-record review), how many audited episodes resulted in feedback (a phone call or visit to the provider), and how many episodes of feedback were delivered to the correct provider (someone directly involved in the prescribing decisions for the patient). The information about correct delivery of feedback will be particularly important, and we expect the majority of the application barriers to occur in this area. This assessment will be made every three months by the research coordinator. If fewer than 90% of episodes of bacteriuria receive audit, or if fewer than 80% of audits are delivered to the correct team within three days, we will reassess our audit and feedback methods. These evaluation elements will be critical for developing implementation and dissemination protocols.

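### Eighteen objective 2 survey items count favourable changes only, so the provider learning measure cannot separate learning from answer noise or from deterioration

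*Protocol article*

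**What the plan says.** Table 2 of the protocol article (under Development of intervention components) sets the measure of meaningful change for each survey domain. Awareness, KA1-KA2, is "Raw number and proportion of respondents changing from NO to YES". Familiarity KF2-KF8 and acceptance AA1-AA2 are "Raw number and proportion of respondents changing from SD or D to SA or A". Familiarity KF9 and the case scenarios OE1-OE6 are "Raw number and proportion of respondents changing from incorrect to correct answers". KF1 is worded differently, beginning "Average increase from". The remaining rows of the table are implementation measures and are not paired survey items.

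The section Analysis plan and sample size for objective 2 takes these definitions over. It will report, by site, the number and proportion of providers "whose survey responses exhibit clinically meaningful change (provider learning), as described in Table 2". It expects 100 providers in each of three groups, "resulting in 300 paired pre/post surveys". It calls the process exploratory. It nevertheless expects the results to inform the efficacy of the intervention from the providers' side and to strengthen the case for dissemination. It also plans to relate the survey attributes to the clinical outcomes, and provider learning to provider demographics.

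Under Study timeline and Table 1, the intervention site is surveyed in years 2 and 3 and the control site in year 3 only. The control-site surveys are meant to show what the surveys alone do to prescribing and to responses.

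**The concern.** A pre/post item can move in either direction. These definitions keep one direction and leave out the other, so the measure has a floor at zero and no way to register loss. Some respondents will answer differently the second time for reasons unrelated to learning: a guess, a slip, or a borderline opinion. Those who happen to move favourably enter the count, and those who move unfavourably vanish.

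The aim begins "Our second objective is to measure increases in", and the stated hypothesis is that knowledge and attitudes will improve. A measure that cannot be negative cannot count against that hypothesis. The planned associations are also exposed. Under pure noise, the less repeatable a group's answers are, the more learners it appears to contain, so a demographic difference in answer consistency could be read as a difference in learning.

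**Working it through.** **The plan's own figure.** The only number given for objective 2 is the survey count: 100 + 100 + 100 = 300 pairs. It reproduces. No test, effect size or answer-reliability figure accompanies it.

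**Items affected (Table 2).** KA1-KA2: 2. KF2-KF8: 7. KF9: 1. AA1-AA2: 2. OE1-OE6: 6. Total 2 + 7 + 1 + 2 + 6 = 18. KF1 is set aside because it is an average rather than a one-way count. The table does not say how items within a group are combined, so the check is per item.

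**No-learning model.** Each respondent has a fixed true answer, favourable for a share p. Each recorded answer is wrong with probability e, independently before and after. The value of e is assumed.

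- Unfavourable to favourable: p × e(1-e) + (1-p) × (1-e)e = e(1-e)
- Favourable to unfavourable: p × (1-e)e + (1-p) × e(1-e) = e(1-e)
- Net change: 0, whatever p and e are

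| e (assumed) | Scored as learners per 100 | Reversals per 100, uncounted | Learners over 300 pairs | Net |
|---|---|---|---|---|
| 0.05 | 0.05 × 0.95 = 4.75 | 4.75 | 14.25 | 0 |
| 0.10 | 0.10 × 0.90 = 9 | 9 | 27 | 0 |
| 0.20 | 0.20 × 0.80 = 16 | 16 | 48 | 0 |

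Pure guessing on a two-option item (e = 0.50) gives 25 per 100.

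**Simulation check.** There were 4,000 runs with n = 100 and p = 0.5. Mean favourable counts were 4.7, 9.0 and 15.9 per 100 at e = 0.05, 0.10 and 0.20. Mean net change lay between -0.12 and +0.03 per 100. An exact McNemar test at the 5% level rejected in 1.8%, 3.1% and 2.9% of runs, so the net paired measure does not manufacture learning under this model.

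**Deterioration.** Let the true favourable share fall from 60% to 50%: 50% stay favourable, 10% lose, 40% stay unfavourable, nobody gains. Take e = 0.10.

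- Favourable moves: 0.50 × 0.09 + 0.10 × 0.01 + 0.40 × 0.09 = 0.045 + 0.001 + 0.036 = 8.2%
- Unfavourable moves: 0.50 × 0.09 + 0.10 × 0.81 + 0.40 × 0.09 = 0.045 + 0.081 + 0.036 = 16.2%
- Net: 8.2 - 16.2 = -8.0 points

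The Table 2 measure would report 8.2% learners here, close to the 9% it reports when nothing changes.

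**The case against.** The strongest reply has four parts.

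- **Exploratory status.** The objective 2 survey items carry no test and no significance level. This stands: no type I error rate is breached, and the objective 1 clinical results do not depend on these counts. It does not change what the count measures.
- **A comparator is planned.** The year 3 control surveys have a stated purpose that includes the effect on responses, and proportions will be calculated at each site with the same one-way measure. This stands in part. Background switching could be read off for year 3. Year 2, when individual feedback is delivered, has no control survey, and the analysis section states no subtraction of the control-site proportion.
- **Silence is not exclusion.** A condensed article may leave discordant tables and paired intervals to a fuller plan. That is fair for intervals and tests. The outcome definition, however, is stated here, and it names one direction.
- **The noise level is unknown.** This stands, and it is why the size is shown only as a range over e.

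A reader might go further and infer that the count must be positive. It need not be: it is zero if nobody switches. A reader might also multiply across the 18 items to say that most respondents would show at least one chance change. Neither Table 2 nor the analysis section defines a learner that way, and the multiplication assumes independent items within one respondent. Nor should chance switching be modelled with one probability in both directions away from a 50% start. With 70% starting unfavourable and 20% switching, 14 per 100 move up and 6 move down, a net of +8, which is not a no-change scenario.

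**Conclusion.** The point holds for 18 items. As defined, the measure is never negative, is above zero in expectation whenever answers are not perfectly repeatable, and can look much the same whether knowledge is stable or falling. Under no learning it scores 4.75 to 16 per 100 providers per item for assumed error rates of 0.05 to 0.20, with equal reversals uncounted. These sizes rest on two answer states, independent errors and the same error rate at both surveys; the direction needs only imperfect repeatability. The documents do not support saying that objective 2 will report learning whatever happens, or that the main clinical conclusion is affected. Because the objective is exploratory and a year 3 control survey exists, the weight is moderate. It is still worth correcting, because the count is labelled learning and is meant to support claims about efficacy and dissemination.

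**What to change.** For KA1-KA2, KF2-KF9, AA1-AA2 and OE1-OE6 only (not KF1 or the implementation rows), redefine the Table 2 measure:

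- Report both discordant counts for each item.
- Report net paired change, favourable minus unfavourable moves divided by all paired respondents, with a McNemar-type interval.
- For the planned associations with clinical outcomes and demographics, use a provider-level score: that provider's number of favourable item changes minus unfavourable ones. The group net proportion cannot serve as a provider-level variable.
- In year 3, compare net change between the two sites.
- State that year 2 net change is uncontrolled for the effect of repeating the survey, which netting does not remove.

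The cost is wording in Table 2 and the objective 2 analysis section, plus an extra column per item. The 300 planned pairs supply all the data, and the article describes the surveys as still in development. The downside is that reported learning will look smaller.
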